## STUDY SYNOPSIS

|                                         |                                                                                                                                                                                                                                                                                                                                                                                                                                                                                                                                                                                                                                                                                                                                                                                                                                                                                                                                                                                                                                                                                                                                                                                           |
|-----------------------------------------|-------------------------------------------------------------------------------------------------------------------------------------------------------------------------------------------------------------------------------------------------------------------------------------------------------------------------------------------------------------------------------------------------------------------------------------------------------------------------------------------------------------------------------------------------------------------------------------------------------------------------------------------------------------------------------------------------------------------------------------------------------------------------------------------------------------------------------------------------------------------------------------------------------------------------------------------------------------------------------------------------------------------------------------------------------------------------------------------------------------------------------------------------------------------------------------------|
| Title                                   | Checkpoint inhibitor-induced liver injury                                                                                                                                                                                                                                                                                                                                                                                                                                                                                                                                                                                                                                                                                                                                                                                                                                                                                                                                                                                                                                                                                                                                                 |
| Acronym                                 | ChILI                                                                                                                                                                                                                                                                                                                                                                                                                                                                                                                                                                                                                                                                                                                                                                                                                                                                                                                                                                                                                                                                                                                                                                                     |

| Study centres                           | 
 
Nottingham Digestive Diseases Centre, NIHR Nottingham Biomedical Research Centre, Nottingham University Hospitals NHS Trust and University of Nottingham, Queens Medical Centre, [name]
 
St. George's University of London, Institute of Infection and Immunity [name]
 
Across UK NHS Secondary Care sites (Including Scotland)
 
                                                                                                                                                                                                                                                                                                                                                                                                                                                                                                                                                                                                                                                                                                                                           |
| Objectives                              | 
 
To identify the incidence and risk factors for checkpoint inhibitor-induced liver injury (ChILI) and the association with other adverse reactions (especially colitis) by studying a prospective cohort of well characterized patients undergoing checkpoint inhibitor treatment in the real-world setting.
 
To identify specific phenotypic features associated with checkpoint inhibitor-induced liver injury.
 
To enrol a similarly well-characterised control group of patients who are treated with checkpoint inhibitors but who do not develop ChILI.
 
To collect and store biological samples (blood, urine, stool) from patients with ChILI at 3 time points (the day of liver injury, 1 week and 1 month after). We will perform liver biopsy when it is clinically indicated.
 
To collect and store biological samples (blood, urine and stool) from control patients at a two time points (before starting CPIs and 6 to 14 weeks after commencing treatment)
 
To determine the histological characteristics of the liver in patients with ChILI using available diagnostic samples
 
 |
| Number of participants / tissue samples | 250 in total or 120 completed control cases and 40 DILI cases, whichever occurs earlier.
Plus anonymised liver tissue from up to 75 biopsies                                                                                                                                                                                                                                                                                                                                                                                                                                                                                                                                                                                                                                                                                                                                                                                                                                                                                                                                                                                                                                           |

|                                           |                                                                                                                                                                                                                                                                                                                                                   |
|-------------------------------------------|---------------------------------------------------------------------------------------------------------------------------------------------------------------------------------------------------------------------------------------------------------------------------------------------------------------------------------------------------|
| Diagnosis and main criteria for inclusion | Symptomatic or asymptomatic adults diagnosed with checkpoint inhibitor-induced liver injury OR adults (without symptoms) undergoing checkpoint inhibitor therapy without evidence of ChILI (control group).                                                                                                                                       |
| Duration of study                         | 5 years                                                                                                                                                                                                                                                                                                                                           |
| Description of interventions              | ChILI patients and controls who are on checkpoint inhibitor treatment: Blood, urine and stool samples will be collected at each visit.
For symptomatic patients only: we plan to collect any surplus liver biopsy samples taken as part of clinical care and any archived surplus paraffin sections taken previously as part of clinical care. |
| Statistical methods                       | Descriptive statistics                                                                                                                                                                                                                                                                                                                            |

## ABBREVIATIONS

|         |                                                         |
|---------|---------------------------------------------------------|
| AE      | Adverse Event                                           |
| AR      | Adverse Reaction                                        |
| ALT     | Alanine transaminase                                    |
| ALP     | Alkaline phosphatase                                    |
| CI      | Chief investigator                                      |
| CPI     | Checkpoint inhibitor                                    |
| ChILI   | Checkpoint inhibitors induced liver injury              |
| CMV     | Cytomegalovirus                                         |
| CRF     | Case Report Form                                        |
| DILI    | Drug-Induced Liver injury                               |
| EBV     | Epstein-Barr virus                                      |
| GCP     | Good Clinical Practise                                  |
| HIV     | Human Immunodeficiency virus                            |
| iDILI   | Idiosyncratic drug-induced liver injury                 |
| INR     | International normalized ratio                          |
| irAE    | Immune-related adverse events                           |
| ISF     | Investigator Site File                                  |
| NDD BRU | Nottingham Digestive Diseases, Biomedical Research Unit |
| NIHR    | National Institute of Health Research                   |
| NUH     | Nottingham University Hospitals                         |
| PI      | Principal Investigator                                  |
| PPI     | Public Patient Involvement                              |
| R       | Ratio                                                   |
| REC     | Research Ethics committee                               |
| SAE     | Serious Adverse Event                                   |
| SAFE-T  | Safer and faster Evidence based translation Consortium  |
| SAR     | Serious Adverse Reaction                                |
| SOP     | Standard Operating Procedure                            |
| SUSAR   | Suspected Unexpected Serious Adverse Reaction           |
| TBL     | Total bilirubin                                         |
| TMF     | Trial Master File                                       |
| UAR     | Unexpected Adverse Reaction                             |
| ULN     | Upper limit of normal                                   |
| WHO     | World Health Organisation                               |

# STUDY BACKGROUND INFORMATION AND RATIONALE

## BACKGROUND

Immune checkpoint inhibitors (CPIs) have evolved over the last decade and treatment with a single CPI or a combination of CPIs has extended survival of patients with a variety of epithelial and lymphoid malignancies. The three major targets of CPIs are cytotoxic T-lymphocyte-associated antigen 4 (CTLA-4), programmed cell death protein 1 (PD-1), and its ligand, programmed cell death ligand 1 (PD-L1). They work by blocking immune suppressive ligand-receptor interactions which enhances the anticancer cytotoxic effects of lymphocytes. However, because checkpoint molecules are also involved in immune tolerance, unfavourable reactions to self-antigens potentially occur [1]. CPIs are associated with immune-related adverse events (irAE) in multiple organ systems including liver. Immune-mediated hepatitis is frequently observed in cancer patients treated with CPIs, up to 5% in single agent or 18% in combination therapies [2]. Checkpoint inhibitor-induced liver injury (ChILI) usually develops many weeks or even months after the start of the therapy, thus an early diagnosis of checkpoint inhibitor-induced hepatitis would help guide cancer therapy and management of drug-induced liver injury (DILI).

## RATIONALE FOR CURRENT STUDY:

Despite remarkable progress in the treatment of several advanced malignancies with CPIs, immune mediated adverse events including checkpoint inhibitor-induced liver injury have been a real clinical challenge not only for physicians but also for cancer patients. This is due to the unpredictable nature of liver injury, lack of robust evidence to guide management and the potential consequences of stopping checkpoint inhibitor treatment. Current guidelines (European Society of Medical Oncology) suggest grading of the liver injury based on liver biochemistry test results: grade 1: alanine transaminase (ALT) or aspartate aminotransferase (AST) > 1 to 3 times upper limit of normal (ULN), grade 2 = ALT or AST >3 to 5 ULN, grade 3 = ALT or AST > 5 to 20 ULN and grade 4 = ALT or AST > 20 ULN [3]

Treatment guidelines for checkpoint inhibitor-induced liver injury are based on colitis and auto-immune hepatitis models with high dose corticosteroids being recommended for grade 3-4 liver injury or persistent grade 2 liver injury [3, 4]. However, steroids in cancer patients can cause serious adverse events and recent reports suggest that around 35% of grade 3/4 hepatitis regresses spontaneously without intervention [5, 6].

The immune-mediated liver injury induced by checkpoint inhibitors is much more frequent, a new and incompletely understood category of hepatotoxicity and distinct from other types of drug induced liver injury (DILI) such as direct or idiosyncratic DILI. Recent evidence suggests that ChILI is primarily mediated by CD8+ T cells, and it is associated with increased T cell activation and infiltration in the liver and with a characteristic histopathologic feature of necrotic/degenerative hepatocytes surrounded by ring-like T cell clusters [7]. This is different from direct chemically-induced, hepatocyte-intrinsic cell damage and death where hepatocyte cell death is typically the primary initiator of the inflammatory response [8]. This histologic feature is also different from autoimmune hepatitis or idiosyncratic DILI in humans [9].

Candidate biomarkers are being investigated to identify diagnostic, prognostic and mechanistic biomarkers of idiosyncratic DILI [10, 11]. A series of robust genome wide association studies (GWAS) in the past decade have demonstrated the association of HLA alleles and other immune related gene polymorphism such as protein tyrosine phosphatase nonreceptor type 22 gene (*PTPN22*) with DILI [12-14].

A variety of approaches have been explored to identify biomarkers that are associated with efficacy in checkpoint inhibitor treated patients. These include immunophenotyping [15-17], cytoscore (cytokine profile) [18, 19], immune gene signature [20-26], TCR clonality analysis [27, 28], immunoscore, multiplex IHC of tissues and PD-L1 expression in tumour cells and associated immune cells [29-31]. These pharmacological changes can occur in peripheral circulation and/or tissues. While there have been some successes in CPI efficacy biomarkers, there are limited reports on identifying biomarkers for checkpoint inhibitor related adverse events. It is believed that the anti-tumor efficacy of CPI is mediated through its pharmacology- the enhanced T cell immune response against tumor antigens. Similarly, irAEs secondary to checkpoint inhibitors are also mediated via CPI pharmacology, likely through augmented immune response against self-antigens. And it appears there is an association between irAEs with efficacy in CPI treated patients [32]. Therefore, it is highly possible that biomarkers for CPI irAEs can also be identified in some if not all the approaches/assays described above. In fact, there has been some promise in identifying gene signatures for CPI related colitis [33]. In a monkey CPI-mediated irAE model, there was markedly increased proliferation and activation of CD4 and CD8 T cells and increased percentages of memory T cells, increased infiltration into tissues of predominant T cells, increased serum cytokines, and identified immune gene signatures such as T cell activation, APC activation and antigen presentation, and immune cell trafficking [34].

The data regarding the incidence and risk factors for this critical phenomenon is lacking. Therefore, we need 'in-depth phenotyping' together with data from control group exposed to CPIs to develop refined algorithms incorporating CPI-related factors, host genetic and environmental risk factors that would enable us to pre-empt ChILI. Deeply phenotyped cohorts with biological samples are essential for the development and validation of novel diagnostic/ prognostic markers [35] so that appropriate treatment guidelines can be developed for patient benefit.

Research has found that certain immune cell types are associated with drug induced liver injury (DILI) [36] and it was demonstrated that blood immune cell characteristics can indicate an autoimmune response to liver damage [37]. As CPIs modulate immune response, the immunological effect might play an important role in ChILI and predict its occurrence. Additionally, immunological analysis will enable researchers to establish markers which can be used to predict future DILI responses [38].

## **STUDY OBJECTIVES AND PURPOSE**

### **PURPOSE**

The purpose of the study is to identify the incidence of checkpoint inhibitor-induced liver injury (ChILI), the specific phenotypic features, and the risk factors associated with ChILI in addition to its relationship with other adverse reactions (especially immune-mediated colitis). It will enable us to obtain a better understanding of the mechanisms underlying ChILI and to develop methods of preventing ChILI and its consequences.

### Hypothesis:

We hypothesise that checkpoint inhibitor-induced liver injury (ChILI) is determined by factors that modulate cellular and immunological response to the development of ChILI and can be recognised by a combination of markers.

## PRIMARY OBJECTIVE

To collect, store and analyse biological samples and clinical data from two prospective longitudinal cohorts, one includes cancer patients undergoing checkpoint inhibitor therapy and another cohort of patients who developed checkpoint inhibitor-induced liver injury (ChILI).

### Proposal Aims:

1. To establish the incidence of ChILI and other immune-related adverse events over a period of 6-14 weeks following checkpoint inhibitor therapy.
2. To identify and characterise biomarkers associated with the diagnosis of ChILI by comparing biomarkers of patients who developed ChILI with patients who had CPI treatment without developing liver injury with follow up to 14 weeks.

## SECONDARY OBJECTIVES

1. To study the natural history of patients treated with checkpoint inhibitors after developing ChILI.
2. To identify specific phenotypic features associated with ChILI compared to idiopathic auto-immune hepatitis and DILI due to other drugs. This includes histological characteristics, genetic, biochemical and immunological characteristics.
3. To determine association between biomarkers, clinical features and development of ChILI.

## STUDY DESIGN

### STUDY CONFIGURATION

It is a multi-centre study which contains four parts, two parallel longitudinal prospective cohorts as outlined below (cohort of patients before and after CPI treatment and cohort of patients who already had treatment and developed liver injury), a cross sectional case control study to compare biomarkers and a liver histology study.

#### Part 1. CPI cohort study (before & after CPI therapy)

We will prospectively develop a cohort of oncology patients (**cohort study**), with malignant melanoma, renal cell carcinoma, non-small cell lung cancer or any other cancer, receiving single or combination therapy using checkpoint inhibitors (CPIs). Two visits will be undertaken (prior starting CPI therapy and 6-14 weeks after treatment, when collection and storage of biological samples and data (medical, demographic and clinical) will be obtained. Timing of ChILI ranges from 1 – 49 weeks following treatment with a peak around 6 – 14 weeks [5] ,

#### Part 2. ChILI cohort

We will recruit patients who are already on CPI therapy and have developed liver injury (ChILI) which fits DILI criteria (*ALT > 5 ULN OR ALT > 3 ULN plus bilirubin > 2 ULN OR alkaline phosphatase (ALP) > 2 ULN* with accompanying elevations of gamma-

Page 10 of 29

glutamyl transferase (GGT) in the absence of known bone metastases driving the rise in ALP level). We will follow up the natural history of ChILI in these patients for 1 month after enrolment. Biological samples will be taken from these patients at 3 time points (date of reaction, 1 week after and 1 month after).

### Part 3. Cross-sectional case/control study (comparing patients in parts 1 and 2)

We will run a cross-sectional case control study comparing biological samples of patients in the cohort study who did not develop ChILI after 6-14 weeks of CPI treatment (controls) with patients in the second study who developed ChILI (cases). A small percentage of patients in the cohort study (3-18%) will develop ChILI and will be added to the cases; they will have 4 visits in total (one prior CPI treatment and 3 visits following reaction). We will compare samples from visit 2 in controls (after 6-14 weeks of treatment without developing ChILI) and visit 1 in cases (time of reaction).

[figure not shown]

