#### Control Group:

Consecutive patients with cancer who have clinical indication to start checkpoint inhibitors will be approached for consent to be enrolled in the study. We will enrol 120 consecutive patients who will be identified as controls. A small proportion of patients will develop ChILI following their checkpoint inhibitor treatment and will be classified as cases.

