### **Exclusion criteria**

Anyone with any of the following conditions will not be included in the study:

- Patients who are treated with cytotoxic chemotherapy concurrently with checkpoint inhibitors.
- On the judgement of CI that the person has certain alternative explanation to the acute event (rather than ChILI).

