## STATISTICS

### Statistical analysis

- We will calculate the incidence of ChILI and other irAE in the cohort group.
- We will describe demographic and clinical data for the enrolled participants using descriptive statistics, mean  $\pm$  standard deviation (SD) for continuous measurements and frequencies and percentiles for categorical data. We will compare patients' pathological and clinical characteristics using Chi-square test for categorical variables and Wilcoxon/Kruskal-Wallis test for the continuous variables.  $P < 0.05$  will be considered statistically significant.
- We will assess the accuracy of the biomarkers for ChILI detection and predicting prognosis using receiver operating characteristic (ROC) curve and the area under the ROC curve (AUC) with 95% confidence interval (CI).
- We will assess the correlation of biomarkers with ALT using Pearson's  $r$  coefficient.

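### Part 3 sets out no contrast between ChILI and ChILI-free patients with another immune-related reaction, so it cannot show that a marker is specific to ChILI

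*Protocol*

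**What the plan says.** **Control definition.** Part 3 compares cases at visit 1 (the reaction) with cohort patients at visit 2, "comparing biological samples of patients in the cohort study who did not develop ChILI after 6-14 weeks of CPI treatment (controls". Aim 2 under Proposal Aims has the same structure: "comparing biomarkers of patients who developed ChILI with patients who had CPI treatment without developing liver injury with follow up to 14 weeks". Neither sets a condition on other irAEs.

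**Enrolment.** The Control Group section states "We will enrol 120 consecutive patients who will be identified as controls". The Exclusion criteria name concurrent chemotherapy and an alternative explanation for the acute event, and do not mention other irAEs. The synopsis describes controls as "adults (without symptoms) undergoing checkpoint inhibitor therapy without evidence of ChILI (control group", a condition on symptoms that the eligibility section does not repeat.

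**Other irAEs.** Their incidence is part of the first primary outcome, and the Statistical analysis section says "We will calculate the incidence of ChILI and other irAE in the cohort group". Their association with ChILI is a secondary outcome. Neither is linked to the biomarker comparison.

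**Shared biology.** The rationale says that "irAEs secondary to checkpoint inhibitors are also mediated via CPI pharmacology, likely through augmented immune response against self-antigens".

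**What is to be claimed.** A synopsis objective reads "To identify specific phenotypic features associated with checkpoint inhibitor-induced liver injury". Biomarkers associated with the diagnosis of ChILI are a primary outcome, and the Statistical analysis section plans ROC curves and AUCs with 95% confidence intervals for ChILI detection.

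**The concern.** Every case in Part 3 has an active irAE, namely the liver injury. Controls are whichever cohort patients did not develop ChILI: some will have had another irAE and the rest none. A difference between the groups may reflect liver injury or immune activation of any kind, and a single contrast cannot separate the two.

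The protocol's own reasoning makes this more than theoretical. It expects irAE markers from immunophenotyping, cytokine and gene-signature approaches, and it cites early success with signatures for colitis. Study Management plans cytokines, immune-cell typing and single-cell RNA sequencing. It also plans markers drawn from earlier drug-induced liver injury studies (microRNAs, K18, MCSFR), so the concern weighs most on the immune assays.

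What is at stake is interpretation. A marker raised equally in colitis and in ChILI could be presented, with a respectable AUC, as a marker of ChILI.

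**Working it through.** **Plan's own figure.** The 40 cases and 120 controls rest on availability. There is no power, effect size or target AUC to reproduce. For scale, a two-sided 5% comparison of two means with 40 v 120 has 78% power at 0.5 SD and 99% at 0.8 SD.

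**Inputs from the protocol.** 40 cases and 120 controls (Sample size and justification); Wilcoxon test, P<0.05 and AUC (Statistical analysis). Two-sided testing is assumed.

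**Inputs assumed.** A normally distributed marker shifts by *d* SD in anyone with any irAE and has no liver-specific effect. A share *q* of controls has another irAE. The protocol gives neither *d* nor *q*, so ranges are shown.

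**Formula.** A case compared with an irAE-free control gives Φ(d/√2). A case compared with an irAE-positive control gives 0.5. Hence

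AUC(pooled) = 0.5q + (1 − q)·Φ(d/√2).

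Φ(d/√2) is 0.638, 0.714 and 0.760 for d = 0.5, 0.8 and 1.0. Example, d = 1.0 and q = 0.3: 0.5 × 0.3 + 0.7 × 0.760 = 0.150 + 0.532 = 0.682.

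**General marker against the pooled controls** (AUC by formula; percentage with P<0.05 from 2,000 simulated studies, 40 v 120):

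| Share q (number of 120) | d = 0.5 | d = 0.8 | d = 1.0 |
|---|---|---|---|
| 0 (0) | 0.638; 75% | 0.714; 99% | 0.760; 100% |
| 10% (12) | 0.624; 66% | 0.693; 97% | 0.734; 99.9% |
| 20% (24) | 0.611; 55% | 0.671; 91% | 0.708; 99% |
| 30% (36) | 0.597; 44% | 0.650; 82% | 0.682; 96% |
| 50% (60) | 0.569; 26% | 0.607; 55% | 0.630; 72% |

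At q = 80% and d = 0.5 the figures fall to 0.528 and 7%.

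**Same marker against other-irAE controls only.** AUC is 0.50, and P<0.05 occurs in about 5% of studies at every *q* and *d*. This is the contrast that tells a general marker from a liver-specific one.

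**Direction.** Down each column the AUC falls as *q* rises. Irrespective of *d*, irAE-positive controls dilute a general marker, and restricting the controls to irAE-free patients would give it the highest AUC.

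**What the added contrast can detect.** For a truly liver-specific marker shifted by 0.8 SD, power with 40 cases (normal approximation) is 68%, 87%, 94% and 98% against 12, 24, 36 and 60 other-irAE controls. With only 12 such controls, simulation (3,000 studies, Wilcoxon) shows that a truly specific marker misses P<0.05 in about 22%, 44% or 66% of studies when its true AUC is 0.75, 0.70 or 0.65. With 6 such controls, about 47% miss even at 0.75.

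**The case against.** **The pooled group is a sound comparator.** Consecutively enrolled ChILI-free patients are a natural reference for detecting ChILI among people on these drugs, and dependence of the AUC on their case mix is ordinary. This stands, and the pooled comparison should remain the main one.

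**Specificity already has named comparators.** Secondary objective 2 sets ChILI against autoimmune hepatitis and other-drug liver injury, covering histological, genetic, biochemical and immunological features. That is correct, and Part 3 nowhere claims that its markers are absent in colitis. But those comparators are other liver diseases. They cannot show whether a marker reflects the liver or checkpoint-inhibitor immune toxicity in any organ.

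**The study is mechanistic.** The sample-size section disclaims evaluating the performance of specific biomarkers. The Statistical analysis section nonetheless plans AUCs for ChILI detection, and a mechanistic account of ChILI also needs this distinction.

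**It could be left to the SAP.** An analysis plan that is not shown may split the controls by irAE status. That limits the point to what the protocol fixes: the comparator in Part 3 and aim 2, stated without this contrast.

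**Two stronger readings are not supported.** A reader might infer that mixing controls with and without other irAEs creates the false signal; the arithmetic shows the reverse. A reader might also infer that a general marker will be reported as a ChILI marker. It can be, but how often depends on an irAE share and a shift that the protocol does not give, and on whether irAEs are still active at visit 2.

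**Conclusion.** The point holds as a gap in what Part 3 can conclude. With controls defined only by the absence of ChILI, and no contrast with ChILI-free patients who had another irAE, neither a significant difference nor the AUC shows that a marker is specific to liver injury.

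Across the tabulated shares of 10% to 50% and shifts of 0.5 to 1.0 SD, a purely general marker would show an AUC of 0.57 to 0.73 and reach P<0.05 in 26% to 99.9% of studies. These figures assume normality and an equal shift in all irAEs, still present when the controls are sampled. They illustrate the mechanism and do not predict the trial's results.

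The synopsis wording about symptoms adds an ambiguity. Controls are enrolled before treatment, so their symptoms at visit 2 cannot be known at enrolment. If the phrase means that patients with symptomatic irAEs are left out, the pooled group moves towards the q = 0 row and the useful comparator shrinks.

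The pooled comparison is not invalid. The case is for a cheap addition and restraint in the word *specific*.

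**What to change.** 1. Keep all ChILI-free cohort patients as the main Part 3 control group.
2. Using the irAE status already needed for the first primary outcome, also report each marker's difference and AUC with 95% confidence interval for (a) ChILI v controls with another irAE, active at visit 2 where known, and (b) ChILI v controls with no irAE.
3. Call a marker ChILI-specific only if contrast (a) supports it. Otherwise state that specificity is not established. Do not conclude from a non-significant result in (a) that the marker is one of irAEs in general: with 12 such controls that would be wrong in about 22% of studies for a specific marker with a true AUC of 0.75, and more often for weaker ones.
4. Reconcile the synopsis condition on symptoms with consecutive enrolment before treatment, and state whether patients with other irAEs remain controls.

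**Cost.** A sentence or two in Part 3 and in Statistical analysis, one correction to the synopsis, and additional analyses of samples and data already planned; no new recruitment. The downside is that contrast (a) rests on a subset of unknown size, so its intervals will be wide and its power may be low.
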